# Biofeedback combined with percutaneous electrical pudendal nerve stimulation for the treatment of low anterior rectal resection syndrome: a study protocol for a randomized controlled trial

**DOI:** 10.1186/s13063-024-08300-9

**Published:** 2024-07-02

**Keywords:** Rectal cancer, Low anterior rectal resection syndrome (LARS), Percutaneous electrical pudendal nerve stimulation, Biofeedback, LARS score, Quality of life, Randomized controlled trial

## Abstract

**Background:**

Low anterior resection syndrome (LARS) is a distressing condition that affects approximately 25–80% of patients following surgery for rectal cancer. LARS is characterized by debilitating bowel dysfunction symptoms, including fecal incontinence, urgent bowel movements, and increased frequency of bowel movements. Although biofeedback therapy has demonstrated effectiveness in improving postoperative rectal control, the research results have not fulfilled expectations. Recent research has highlighted that stimulating the pudendal perineal nerves has a superior impact on enhancing pelvic floor muscle function than biofeedback alone. Hence, this study aims to evaluate the efficacy of a combined approach integrating biofeedback with percutaneous electrical pudendal nerve stimulation (B-PEPNS) in patients with LARS through a randomized controlled trial (RCT).

**Methods and analysis:**

In this two-armed multicenter RCT, 242 participants with LARS after rectal surgery will be randomly assigned to undergo B-PEPNS (intervention group) or biofeedback (control group). Over 4 weeks, each participant will undergo 20 treatment sessions. The primary outcome will be the LARS score. The secondary outcomes will be anorectal manometry and pelvic floor muscle electromyography findings and the European Organization for the Research and Treatment of Cancer Quality of Life Questionnaire-Colorectal 29 (EORTC QLQ-CR29) scores. Data will be collected at baseline, post-intervention (1 month), and follow-up (6 months).

**Discussion:**

We anticipate that this study will contribute further evidence regarding the efficacy of B-PEPNS in alleviating LARS symptoms and enhancing the quality of life for patients following rectal cancer surgery.

**Trial registration:**

Chinese Clincal Trials Register ChiCTR2300078101. Registered 28 November 2023.

## Introduction

### Background and rationale {6a}

Colorectal cancer (CRC) ranks as the world’s third most prevalent cancer, with the rectum affected in approximately half of the cases [1]. Surgical procedures remain the primary treatment for rectal cancer, offering opportunities for anus-preserving surgeries and improved quality of life using advanced medical technologies such as the Da Vinci robot [2]. However, postoperative complications include low anterior resection syndrome (LARS) that occurs in 25–80% of patients, characterized by fecal incontinence, urgency in bowel movements, and increased frequency of bowel movements [3]. Although these symptoms stabilize within 6 months to 1 year postoperatively, they often tend to persist [4, 5] and may significantly affect the patient’s life, sometimes even necessitating colostomy. Consequently, effective LARS treatments are urgently required.

LARS pathogenesis involves multiple theories, including anal internal sphincter dysfunction, reduced rectal sensitivity, the absence of the rectoanal inhibitory reflex, and reduced rectal compliance [6]. Nerve damage during the low anterior resection process might lead to new rectal innervation, exacerbating the LARS symptoms [7]. Current treatments encompass non-surgical options, such as pharmacotherapy, biofeedback, transanal electrical stimulation, and enema therapy, as well as surgical approaches, such as artificial sphincter replacement, colostomy, and neurostimulation therapy. Oral serotonin receptor antagonists, effective in treating diarrhea-predominant irritable bowel syndrome, are employed to alleviate LARS symptoms such as fecal incontinence and urgency;[8] however, further clinical trials are warranted for validation. Enema therapy effectively manages fecal incontinence but may have potential side effects, including rectal bleeding, perianal pain, anal fissures, abdominal discomfort, and colonic perforation [9]. Although artificial sphincter replacement is suitable for severe anal incontinence, the high cost and postoperative complications limit its application. Colostomy is the last treatment option in cases where other treatments fail; however, it imposes significant psychological stress on patients. Biofeedback may be effective in managing fecal incontinence by using transanal probes to track activity changes in the pelvic floor muscles, guiding patients through Kegel exercises, and delivering precise electrical stimulation for pelvic muscle recovery [10]. However, patients might find it difficult to follow Kegel exercise instructions, which could impede the treatment efficacy. Additionally, surface electromyography (EMG) stimulation via the anus provides an indirect and comparatively weaker therapeutic effect than deeper direct muscle stimulation, potentially offering less favorable outcomes [11].Recently, neural electrical stimulation therapies, such as sacral nerve stimulation and pudendal nerve stimulation, have become focal points in LARS treatment. Multiple clinical studies have affirmed their positive effects in treating fecal incontinence, LARS, and other defecation disorders [12, 13]. However, the implantation of electrodes in the body required in both stimulation methods poses issues, such as battery replacement, high costs, postoperative infections, and surgical failures [14]. Percutaneous electrical pudendal nerve stimulation (PEPNS) is an innovative technique developed by Wang Siyou [15]. It involves the insertion of extended needles through the lower sacral points on the skin confirmed on transverse computed tomography of the coccygeal apex, showing the needle tips located in the ischiorectal fossa proximal to the pudendal nerve within the Alcock canal [16]. The rectum and sphincter are regulated by nerves originating from the pelvic plexus located in the lower abdomen. This plexus includes both sympathetic fibers from the presacral nerves and parasympathetic fibers from the S2–S4 spinal segments, forming the neural basis for controlling functions of the rectum and sphincter muscles. The pudendal nerve is essential for the perineal sensation and voluntary movements of the pelvic floor muscles, especially the control of the external anal sphincter. It originates from the S2–S4 sacral spinal segments and divides into the following three branches in the Alcock canal: the inferior rectal branch, the perineal branch, and the dorsal nerve of the clitoris or penis. The inferior rectal branch innervates the external anal sphincter, levator ani, lower anal canal, and perianal skin [17]. The suggested mechanism involves continual electrical stimulation of the pudendal nerve alongside the merging of incoming nerve fibers from the anorectal region at the common neurons in the S2-S4 spinal segments, which regulate the visceral nerves [18, 19]. Moreover, pudendal nerve electrical stimulation can increase resting pressure in the sphincter, thus enhancing bowel control. [20]

Therefore, the application of PEPNS along with biofeedback could be an effective and economical non-surgical treatment for LARS. This study aims to conduct a randomized controlled trial (RCT) to compare the efficacy and safety of this combined approach with biofeedback alone.

### Objectives {7}

The aim of this study is to evaluate the short-term (1 month) and long-term (6 months) effects of B-PEPNS on alleviating symptoms of LARS and improving the quality of life for patients undergoing rectal cancer surgery.

### Trial design {8}

This is a two-center, randomized controlled, partially blinded superiority study with a two-group parallel design, wherein data from two separate groups will be analyzed over an 8-week treatment period (from February 5, 2023, to January 31, 2025). In total, 242 LARS patients will be randomly allocated to the intervention and control groups in a 1:1 ratio. All procedures are detailed in Fig. 1 according to the Standard Protocol Items: Recommendations for Interventional Trials guidelines. [21]

**Fig. 1 Fig1:**
[figure not shown]
Flow chart of the study participants

## Methods: participants, interventions, and outcomes

### Study setting {9}

Patients will be recruited from two tertiary hospitals: Sir Run Run Shaw Hospital (SRRH), affiliated with the Zhejiang University School of Medicine, and the First Affiliated Hospital of Zhejiang Chinese Medical University. Biofeedback sessions will take place at SRRH, while Percutaneous Electrical Pudendal Nerve Stimulation will be administered at the First Affiliated Hospital of Zhejiang Chinese Medical University. Evaluations will be conducted at both institutions.

### Eligibility criteria {10}

#### Inclusion criteria

Age between 18 and 80 years of any sexPresence of persistent defecation dysfunction for at least 1 month following laparoscopic-assisted anal preservation radical surgery for CRC, including cases involving temporary ileal stoma retraction surgeryAdherence to the LARS diagnostic criteria outlined in the international LARS expert consensus [3]Normal preoperative anal function examination without any preexisting defecation dysfunctionGood communication skills and capability to engage actively in intervention procedures and questionnaire surveys

#### Exclusion criteria

Prior inflammatory bowel disease, constipation, irritable bowel syndrome, or other conditions potentially influencing bowel functionPermanent stoma placement for reasons unrelated to CRC surgeryLong-term medications that may significantly affect bowel functionConcurrent severe conditions affecting the heart, liver, kidneys, nervous system, or other organsRecurrence or distant organ metastasis

### Additional consent provisions for collection and use of participant data and biological specimens {26b}

On the consent form, participants are requested to sign indicating their acknowledgment of having received both written and oral information regarding the purpose, methodology, benefits, and risks associated with participating in the trial, as well as their voluntary agreement to participate. Participants are explicitly informed that they retain the right to withdraw their consent at any time without forfeiting any entitlement to treatment, present or future. Moreover, they are queried about their consent for data utilization in the event of withdrawal from the trial. This trial does not entail the collection of biological specimens for storage.

## Interventions

### Explanation for the choice of comparators {6b}

Both the control group and the intervention group will receive the same duration of biofeedback therapy, but the intervention group will also receive additional PEPNS therapy. This study will demonstrate the synergistic effects of PEPNS in alleviating LARS symptoms and improving patients’ quality of life in conjunction with biofeedback.

### Intervention description {11a}

(1) Intervention group (B-PEPNS)

#### Patients in this group will receive a combined treatment of biofeedback and PEPNS

Biofeedback Therapy: Patients will be positioned in a semi-supine stance at a 120° angle, maintaining relaxed arms and extended legs. Following lubrication, electrode probes will be carefully inserted into the anal canal and rectum, linking to a biofeedback stimulator. Patients will receive guidance to engage specific muscles—primarily the anal and pelvic floor muscles—while consciously avoiding the activation of the abdominal or thigh musculature. The therapy regimen will involve a dual-step process with initial training (Kegel template training) comprising controlled contractions for 10 s, followed by a 10-s rest period, guided by pelvic floor EMG data. Subsequent sessions will include electrical stimulation training, contingent upon preset thresholds correlated with pelvic muscle contractions. This 30-min therapy session will be conducted once daily from Monday to Friday over 4 weeks, with rest on the weekends.

PEPNS: Patients will be asked to assume a prone position. Four specific points along the caudal sacrum will be selected in alignment with the pudendal nerve direction. The puncture sites have been described in detail in the illustration in our previous study [22]. We will target the upper points (adjacent to the sacrococcygeal joint symmetrically on both sides) and lower points (located 1 cm from the coccyx tip on each side). Long acupuncture needles (0.4 mm × 100 mm; Suzhou Shenlong Medical Apparatus Factory, Suzhou, China) will be vertically inserted 75–90 mm deep at the upper points and diagonally toward the lateral side (in the direction of the ischiorectal fossa) at a depth of 90–95mm at the lower points. These needles will be connected to electrodes on a G6805 electro-acupuncture apparatus to deliver continuous electrical stimulation at a frequency of 2 Hz and intensity adjusted to each patient’s tolerance. Each PEPNS session, lasting 60 min, will be conducted Monday to Friday for 4 weeks, with rest on the weekends.

(2) Control group (biofeedback alone)

Patients in this group will exclusively undergo biofeedback treatment, following the same procedures detailed previously for the intervention group.

Licensed physical therapists with at least 3 years of experience will deliver biofeedback treatment for both the intervention and control group patients. Acupuncturists with a minimum of 2 years of acupuncture practice will perform PEPNS for the intervention group. Since biofeedback and PEPNS are part of their routine practice, they do not require additional training.

### Criteria for discontinuing or modifying allocated interventions {11b}

If a needlestick infection occurs during PEPNS, the treatment will be delayed, and antibiotics will be administered. If symptoms improve within 1 week, treatment will continue. If symptoms do not improve within 1 week, or if another infection occurs after improvement, treatment will be terminated. Meanwhile, this should be reported as an adverse event. And if any other unforeseen serious side effects occur, the intervention will also be terminated.

### Strategies to improve adherence to interventions {11c}

Adherence enhancement strategies will be implemented throughout the trial period. After 1 week of treatment, all patients will be directly scheduled for their next week’s treatment session. At the conclusion of each weekly treatment session, we will engage in discussions with patients regarding their treatment experience and remind them of the importance of adhering.

### Relevant concomitant care permitted or prohibited during the trial {11d}

Throughout the trial period, participants with background diseases, regardless of their allocation, are allowed to take relevant medications as needed. However, participants, regardless of their allocation, are prohibited from other treatments related to LARS, such as oral loperamide and enema.

### Provisions for post-trial care {30}

We will provide free medical treatment to intervention-related harms, such as needle-related infections.

### Outcome {12}

Before commencing the treatment regimen, comprehensive patient information will be compiled, including demographic data, tumor metrics, surgical specifics, and any prior radiotherapy or chemotherapy received. Patients will undergo evaluations using the LARS and European Organization for Research and Treatment of Cancer Quality of Life Questionnaire-Colorectal 29 (EORTC QLQ-CR29) scoring systems along with anorectal manometry (ARM) and pelvic floor EMG assessments. These evaluations will be conducted at the following three key times: baseline, post-intervention (at 1 month), and during follow-up (at 6 months).

#### Primary outcome

The primary outcome will be defined as the improvement rate. This will be determined by assessing the change in the LARS scores for each patient. The improvement rate will be calculated as follows:

Improvement rate (%) = [(LARS score before treatment − LARS score after treatment) ÷ total score before treatment] × 100

The treatment will be considered effective if the improvement rate surpasses 25%.

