### Methods in analysis to handle protocol non-adherence and any statistical methods to handle missing data {20c}

In cases where the lost-to-follow-up rates are below 20%, we will conduct an intention-to-treat analysis. Missing values will be replaced using single imputation procedures with the group mean.

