The selected outcome measures are based on their validity and reliability. The LARS score has been tested in the Chinese population and measured bowel dysfunction in patients after CRC surgery [23, 28]. This scoring system measures various aspects of postoperative bowel function, such as fecal incontinence, urgency of bowel movements, and bowel frequency, aiding physicians in evaluating the recovery and quality of life of patients postoperatively. A higher score indicates a more severe impact on the patient’s postoperative bowel function. ARM, the anorectal pressure measurement device, evaluates the strength, coordination, and reflex mechanisms of the anal sphincter muscles, pivotal for maintaining continence. [29]

The EORTC QLQ-CR29 is an evaluative tool used to gauge the multifaceted dimensions concerning treatment aspects and their influence on the daily lives of CRC patients. This comprehensive questionnaire covers distinct areas, encompassing symptomatic experiences, functional constraints, and emotional well-being directly associated with the ailment and its therapeutic interventions. Through its systematic inquiry method, the EORTC QLQ-CR29 assists in the meticulous assessment and resolution of the diverse array of challenges encountered by individuals undergoing CRC treatment. Its use helps in significantly fostering a more comprehensive and integrated approach toward patient care and therapeutic management strategies. [30]

Pelvic floor EMG is a diagnostic method assessing pelvic muscle activity via electrical signals. It evaluates the muscle strength, coordination, and relaxation patterns in pelvic floor disorders, such as incontinence. EMG aids in facilitating tailored treatments by providing precise muscle function insights, contributing to improved patient care.[31] 

Nevertheless, it is crucial to acknowledge certain limitations of this study, including potential variability in participant adherence and the absence of long-term follow-up data. Additionally, the inability to blind participants and therapists to the chosen treatment methods might introduce bias. However, efforts will be made to ensure independent data collection and processing, aiming to mitigate potential biases as much as possible.

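### Group-mean imputation has no exception for a stoma formed because bowel function failed, so that failure would take the arm's average improvement

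*Protocol article*

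**What the plan says.** Primary outcome (item 12): "The primary outcome will be defined as the improvement rate", the percentage fall in the LARS score from before to after treatment. The same section adds: "The treatment will be considered effective if the improvement rate surpasses 25" per cent. The calculation needs a post-treatment LARS score. Assessments are planned at baseline, 1 month and 6 months.

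Discussion, on the LARS score: "This scoring system measures various aspects of postoperative bowel function, such as fecal incontinence, urgency of bowel movements, and bowel frequency".

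Background and rationale (item 6a): symptoms may persist, "sometimes even necessitating colostomy". Later in the same item: "Colostomy is the last treatment option in cases where other treatments fail".

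Missing data are covered in two places. Item 20c says: "Missing values will be replaced using single imputation procedures with the group mean". Data processing and preliminary steps (item 20a) prescribes last observation carried forward (LOCF) and refers to item 20c for further rules. Neither place distinguishes the reasons for a missing value.

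Concomitant care (item 11d): participants "are prohibited from other treatments related to LARS, such as oral loperamide and enema". The section does not say how the data of someone who receives such a treatment are handled.

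Stomas otherwise appear only in the entry criteria, in the Discussion's remark on when treatment can start, and in the quality-of-life items. No section says how a stoma formed during follow-up enters the primary outcome.

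**The concern.** A stoma formed because bowel function could not be restored is a known bad outcome, but the outcome formula gives it no value. Item 20c would then treat it like a missed visit and fill in the arm's mean improvement. A treatment failure becomes an average improver, and a responder if the arm mean is above 25%.

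A better imputation method would not cure this. Multiple imputation, or a choice between LOCF and the group mean, would still give the patient an imputed improvement. The rule has to sit in the outcome definition. At stake is bias in the treatment contrast. Its direction depends on which arm has more stomas and on which arm means lie above the threshold.

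**Working it through.** **Inputs from the protocol.** Efficacy rates 65.6% and 46.7%, 210 patients, power 0.80, alpha 0.05, 1:1 allocation, 242 after a 15% dropout allowance, 121 per arm (Sample size, item 14); two-tailed tests (item 20a); threshold 25% (item 12).

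**Assumptions.** The stoma share s per arm is not in the documents; 1% to 5% is used. The item 14 rates are taken to hold among patients without a stoma. Group mean is read as the mean improvement rate of the allocated arm. If the raw score were filled instead, the patient's own baseline would also enter.

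**The plan's own figure.** With unpooled variance, n per arm = (1.960 + 0.842)² × (0.656 × 0.344 + 0.467 × 0.533) / 0.189² = 104.3. That rounds up to 105, or 210 in total. Then 210 × 1.15 = 241.5, so 242. Both figures reproduce, and the point does not rest on a sample-size error.

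**Responder rate.** Let p be the rate among patients without a stoma.
- Stoma counted as not effective: p(1 − s).
- Group-mean imputation, arm mean above 25%: p(1 − s) + s.
- Group-mean imputation, arm mean at or below 25%: p(1 − s).

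Equal shares, only the B-PEPNS mean above 25%:

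| s per arm | Difference, stoma as failure | Difference, group mean | Shift |
|---|---|---|---|
| 1% | 64.9 − 46.2 = 18.7 points | 65.9 − 46.2 = 19.7 points | 1 point |
| 2% | 64.3 − 45.8 = 18.5 points | 66.3 − 45.8 = 20.5 points | 2 points |
| 5% | 62.3 − 44.4 = 18.0 points | 67.3 − 44.4 = 23.0 points | 5 points |

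If both means exceed 25% and the shares are equal, s is added to both arms and the difference does not change. If the shares differ, the shift can go either way. With both means above 25%:
- 5% B-PEPNS and 2% control: 16.6 points as failure, 19.6 with the group mean.
- 2% B-PEPNS and 5% control: 19.9 points as failure, 16.9 with the group mean.

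**Mean improvement rate**, which Primary outcome analysis (item 20a) compares by t-test. Let the arm means among patients without a stoma differ by d. Group-mean imputation leaves d unchanged. Scoring stomas as 0% improvement, for illustration only, gives (1 − s)d at equal shares. With assumed means of 30% and 20%:
- 5% in each arm: 28.5 − 19.0 = 9.5 points against 10, a relative change of 5%.
- 5% B-PEPNS and 2% control: 28.5 − 19.6 = 8.9 points against 10.
- 2% B-PEPNS and 5% control: 29.4 − 19.0 = 10.4 points against 10.

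**LOCF.** With assumed scores of 36 at baseline and 26 at 1 month, followed by a stoma, the value carried to 6 months is (36 − 26)/36 = 27.8%, which counts as effective. If only the baseline score exists, the carried value is 0%, which counts as not effective.

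**The case against.** The strongest reply is that the event may hardly occur. The colostomy remarks are background on LARS in general. Treatment lasts 4 weeks, assessments are at 1 and 6 months, and the Discussion expects symptoms to improve and stabilise between 6 months and 1 year. A last-resort operation is unlikely by 1 month and probably rare by 6 months. This stands, and it limits the size of the effect.

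Second, the larger figures use the 25% threshold, whereas Primary outcome analysis compares scores and improvement rates by t-test or Mann-Whitney and names no responder test. This stands too. On the mean improvement rate the effect is about 5% in relative terms at 5% per arm.

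Third, a reader might infer that both missing-data rules reward the failure. The documents do not support that for LOCF, which credits improvement only when a good 1-month score came before the stoma. A patient who goes on to a stoma for failed function would more often have a poor last score.

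Fourth, a reader might infer a serious loss of power. With 1% stomas in the B-PEPNS arm, 5% in control and both means above 25%, the difference falls from 20.6 to 16.6 points, and power at 121 per arm (unpooled variance) from 91% to 75%. The arithmetic is right. But that case needs a control mean above 25%, while a control rate of 46.7% puts the control median at or below 25%. It also starts from an effect larger than the planned 18.9 points.

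Fifth, the ban on other LARS treatments arguably covers colostomy, and rare events are often left to a full analysis plan. Neither removes the point. A ban does not say how the data are scored, and the article itself fixes imputation rules that, read as written, produce the wrong value.

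**Conclusion.** The point holds in a limited form. The rule in item 20c, applied as written, gives a patient whose bowel function failed to the point of a stoma the arm's mean improvement, and counts that patient as effective when the mean exceeds 25%. LOCF does so only after a 1-month improvement above 25%.

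Three assumptions carry this. A stoma leaves no meaningful LARS score, which follows from what the Discussion says the score measures but is not stated. Group mean refers to the allocated arm. Stomas occur at some rate that the documents do not give.

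At an assumed 1–5% per arm, the responder difference moves by about 1 to 5 points if only one arm's mean exceeds 25%. The mean improvement difference changes by about 5% in relative terms at 5% per arm, and in either direction if the arms differ. The effect is probably small at 1 month and modest at 6 months. The documents do not show that the primary result would be materially wrong. They do show a gap that is cheap to close, and that is best closed before anyone sees outcome data by arm.

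**What to change.** Add to the primary outcome definition (item 12) and to item 20c:
- A patient who receives a stoma because of bowel dysfunction before an assessment counts as not effective at that and later assessments.
- In the rank-based comparison of scores the patient takes the worst rank. A value of 0% is not equivalent, because it ranks above patients whose score worsened. A worst rank also does not fit a t-test, so the text should name the rank comparison as the one that includes these patients.
- LOCF and group-mean imputation do not apply to these values.
- Stomas for other reasons are listed by arm.

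The cost is a few sentences in the protocol and analysis plan, plus recording the reason for any stoma at follow-up. The downside is a slightly less favourable responder rate in an affected arm. No treatment or visit changes.
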